**Intervention**

***Eccentric exercise protocol***

The exercise session will be designed in three distinct phases.

1. General Warm-Up: The initial phase will involve a warm-up, focusing on enhancing joint mobility in the lower limbs and engaging in bodyweight strength exercises. This preparatory phase will condition the athletes for the subsequent exercises aimed at inducing DOMS.

2. Intervention Exercises: Participants will engage in a series of three exercises. The cornerstone of this phase will be the encoder-controlled squat exercise. Execution of the squat will be quantified using a linear accelerometer, calibrated to measure 60% participant's one-repetition maximum (1-RM) (González-Badillo et al., 2011).

3. Eccentric Workout Routine: The final phase will encompass the following three exercises:

a) Squat Forward, 10 sets of 10 repetitions at 60% of the participant’s 1-RM, a value established during the pre-study workout session.

b) Bulgarian Squat, 3 sets of 10 repetitions for each leg, with an option to add an additional 5 or 10 kg of weight.

c) Forward Beam (Split), 3 sets of 10 repetitions on each leg, with the possibility of adding 5 to 10 kg of weight.

***Protocol for Transcranial and Peripheral Electromagnetic Stimulation in the Study***

Control (Cont) Group: The electromagnetic stimulation machine will be positioned identically as in the active treatment groups. However, the machine will be turned off, and pre-recorded sounds of the machine's operation will be playing during the treatment session.

Super Inductive (P) Group: The PES treatment will be administered, following the Long-Term Potentiation protocol. This protocol will entail five stimulations at 100 Hz, each lasting for 5 seconds, interspersed with 55-second rest intervals. The total stimulation time for this group will be 10 minutes.

Transcranial Stimulation (T) Group: This group will receive TES treatment involving 2000 pulses administered over a minimum duration of 20 minutes, targeting the cortical area M1.

Combined Stimulation (Comb) Group: Participants in this group will receive a combination of both PES and TES treatments, with the total stimulation time extending to 30 minutes.

In all groups, the treatment will start one hour post the eccentric exercise session, aligning with the onset of fatigue, time T2 in the study.

The TES and PES treatments will be administered using a MagRex magnetic stimulator equipped with a ring-shaped coil / 8-shaped coil (MR Inc., Republic of Korea, http://www.mrev.co.kr).

**Primary Outcome Measure: Surface Electromyography**

In this research, the mDurance® EMG system (mDurance Solutions SL, Granada, Spain) will be employed. This portable surface EMG (sEMG) system integrates three components: sensors, mobile computing, and a cloud-based data analysis framework.

1. First Sensor – Rectus Femoris (RF) Evaluation: Participants will be positioned on a stretcher, with knees slightly flexed and the trunk leaning backwards. Electrodes will be placed at the midpoint between the anterior superior iliac spine (AIS) and the top of the patella. The ground electrode will be positioned on the patella.

2. Second Sensor – Vastus Lateralis (VL) and Vastus Medialis (VM) Activity Recording: For the VE, electrodes will be positioned at two-thirds of the distance along the line from the EIAS to the lateral part of the patella. For the VM, electrodes will be placed at 80% of the distance from the EIAS to the anterior border of the internal lateral ligament.

Surface muscle activity will be captured using two bipolar sensors provided by Shimmer Research Ltd, Dublin, Ireland. Data recording and transmission will be facilitated by the mDurance® mobile application, installed on a Galaxy A7 Android Tablet (ZtotopCase, Suwon, South Korea).

**Secondary Outcome Measures:**

***Dynamometry***

The study will use strength dynamometry, using an ActiveForce 2 device (Activbody, San Diego, CA). Maximal isometric strength of the quadriceps will be measured during knee extension while the participant is seated, with the knee positioned at a 90-degree angle. A motion-limiting strap will be applied to the middle third of the leg. The participants will be required to sustain the contraction for 5 seconds, repeating the process twice with a 5-minute rest interval between contraction.

***Counter Movement Jump***

Participants will perform the CMJ with their hands on their hips, executing a knee flexion followed by a rapid extension to achieve maximum jump height. The CMJ will be recorded using the validated My Jump 2 application, capturing each jump in slow motion at 240 frames per second with an iPad Pro 10. The tablet will be positioned consistently for each recording to ensure stable and reliable data capture.

**Statistical analysis**

SPSS v.29 (IBM, Armonk, NY, USA) will be used to perform statistical analysis. Normal distribution of data will be assessed using histograms and the Shapiro-Wilk test. Variables with a p-value less than <0.05 will be considered to have a non-normal distribution, while variables with a p-value greater than 0.05 will be considered to have a normal distribution. To describe the sample, the mean and standard deviation will be reported for normally distributed variables, while the median and interquartile range will be reported for non-normally distributed variables. Independent t tests or Mann-Whitney U tests will be used to compare means between groups at baseline for quantitative variables. When the assumptions are met, a 5x4 (5 measurements x 4 groups) mixed analysis of variance (ANOVA) will be performed, with correction for multiple comparisons using the Bonferroni test. The effect size, expressed as partial eta squared (ηp2​), can be categorized into three ranges: a small effect (0.01), a medium effect (0.06), and a large effect (0.14).

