**STUDY PROTOCOL – DOMS RECOVERY TRIAL**

**Study Design and Setting**

A randomized, controlled, double-blind trial involving young athletes will be performed. The Helsinki ethical guidelines will be followed, and all the participants after receiving a presential explanation of the study’s procedure will complete an informed consent form before starting the study.

Participants will be allocated into one of four distinct groups: the Control group (Cont), which received no intervention; the Super Induction group (P); the Transcranial group (T); and the Combination of Stimulation group (Comb). A neutral location will be designated for administering the treatments, and researchers assigned to the treatment stations will be exclusively involved in administering the interventions.

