**Sample size calculation**

The sample size calculation for the study has been performed using G*Power Software. An F-test was selected for an ANOVA with repeated measures, accounting for within-between interaction. Input parameters included a medium effect size f=0.20, a significance level of 0.05, a power of 0.8, four groups, five measurements, and a nonsphericity correction of 1. The results indicated that a total sample size of 48 participants is required to achieve the sufficient statistical power. To account for potential losses of 10%, the sample size will be increased to 52 participants (13 per group) to compensate for possible dropouts.

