**Randomization**

Randomization of groups will be performed using the randomization function of Microsoft Office Excel (Microsoft Corporation, Redmond, Washington, USA). Participants will be assigned to one of four study groups as described previously. The examiners and the data analyst will be blinded to the participant’s group allocation during the study as a special room will be designed for the participants to receive the treatments.

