**Procedure**

The study's methodology will involve a structured series of five assessment sessions for each participant. A familiarization session will be conducted one week prior to the commencement of the first assessment to acquaint participants with the procedures and equipment.

The assessment session (T1) will be comprehensive, encompassing a range of physiological and biomechanical measurements, such as the collection of creatine kinase (CK) levels, blood lactate concentration, performance in the Counter Movement Jump (CMJ), dynamometry of the quadriceps, surface electromyography (EMG) of the quadriceps, and anthropometric data.

Subsequent sessions will be scheduled at specific intervals post-exercise - namely 1 hour (T2), 24 hours (T3), 48 hours (T4), and 72 hours (T5) after the induction of muscle damage - to track the progression and recovery over time.

The evaluation of muscle damage will be primarily focused on the analysis of blood CK and lactate concentrations, obtained from a pin prick blood samples and will be analyzed using electrophoretic analysis (Lactate Scout Pro, Musimedic S.L Donostia, Spain). To ensure the accuracy of these enzyme measurements, participants will be instructed to abstain from any physical activity for at least two days prior to the study, before the baseline timeline (T1 study time). The participants could resume a normal physical activity after completing the first day (including T1 and T2 study time).

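### Two-group significance tests at baseline do not fit four randomised arms and answer no useful question; separately, T1 would give more precision as a covariate than as one of five response levels

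*Protocol*

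**What the plan says.** The baseline comparison is fixed in the Protocol, Statistical analysis: "Independent t tests or Mann-Whitney U tests will be used to compare means between groups at baseline for quantitative variables". The design has four arms (Study Design and Setting: "Participants will be allocated into one of four distinct groups"), and allocation is random (Randomization: "Randomization of groups will be performed using the randomization function of Microsoft Office Excel").

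T1 is the pre-exercise baseline. Under Procedure, "The assessment session (T1) will be comprehensive, encompassing a range of physiological and biomechanical measurements"; these include CK, lactate, jump performance, quadriceps force, quadriceps EMG and anthropometry.

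The main analysis in the same Statistical analysis section is a mixed ANOVA with five measurements and four groups, so T1 is one of the five response levels. No covariate is named. The Bonferroni correction stands in the ANOVA sentence, not in the sentence on baseline tests. The section does not say what would follow from a significant baseline test.

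**The concern.** There are two separate issues.

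**The baseline tests.** A t test or Mann-Whitney test takes two groups. With four arms the sentence must mean either pairwise testing, up to six tests per variable, or some selection of pairs that is not stated. On either reading the null hypothesis is true by design, because the arms are randomised. A small p-value is then a false alarm. A large one is weak reassurance, because with 13 per arm the tests pass over sizeable gaps.

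**The role of T1 in the outcome model.** With T1 as a response level, T1 enters the group-by-time test through differences from T1. That uses T1 with a fixed weight of one, whatever its correlation with later visits. A covariate uses the weight that the data support, which lowers the variance and removes the part of a chance T1 gap that would otherwise carry into the contrast. With 12 or 13 per arm, precision available without further recruitment is worth having.

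**Working it through.** **Reproducing the plan's sample size.** The inputs in Sample size calculation are "a medium effect size f=0.20, a significance level of 0.05" and "a power of 0.8, four groups, five measurements, and a nonsphericity correction of 1". The correlation ρ between measurements is not given. For the within-between interaction, λ = f²·N·m/(1−ρ), df1 = (k−1)(m−1) and df2 = (N−k)(m−1), with k = 4 and m = 5. At ρ = 0.5 and N = 48:

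- λ = 0.04 × 48 × 5 / 0.5 = 19.2, df1 = 12, df2 = 176, power 0.821.
- N = 44 gives power 0.775.

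So the stated 48 is reproduced at ρ = 0.5, in steps of four. Other values give other totals: 64 at 0.3, 56 at 0.4, 40 at 0.6 and 32 at 0.7. I use 0.5 as the planning value and show a range.

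**False baseline differences.** Simulation under the null, 13 per arm, each test at 0.05, no correction:

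- Six pairwise t tests: at least one p < 0.05 in about 20.5% of runs, with 0.30 false positives expected per variable. Mann-Whitney: 19.4%.
- Each active arm against control only (three tests): 12.5%.

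The number of T1 variables is an assumption. I take 7: CK, lactate, jump, force and EMG of three muscles, leaving anthropometry aside.

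- All pairs, independent variables: 1 − (1 − 0.2048)⁷ = 0.80.
- All pairs, variables correlated at 0.5 (simulated): 0.68.
- Against control only, independent variables: 1 − (1 − 0.125)⁷ = 0.61.
- For comparison, one four-group test per variable: 1 − 0.95⁷ = 0.30.

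**What the tests miss.** With 24 degrees of freedom an observed gap must reach about 2.064 × √(2/13) = 0.81 SD to give p < 0.05. A gap of at least 0.5 SD in either direction has probability 2Φ(−0.5/√(2/13)) = 0.20 for a given pair of arms (0.22 with 12 per arm).

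**Carry-over of a T1 gap.** Given an observed T1 gap of g, the expected chance gap at a later visit is ρg, so the change contrast is shifted by (1−ρ)g in size. For g = 0.5 SD and ρ = 0.5 this is 0.25 SD. Larger gaps shift it by more.

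**Precision.** This assumes equal variances and equal correlations between visits, in units of SD². For one post-treatment visit, the variance of change from T1 is 2(1−ρ) and with T1 as covariate it is 1−ρ². The ratio is (1+ρ)/2.

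| ρ | Change from T1 | T1 as covariate | Reduction |
|---|---|---|---|
| 0.3 | 1.40 | 0.91 | 35% |
| 0.5 | 1.00 | 0.75 | 25% |
| 0.7 | 0.60 | 0.51 | 15% |
| 0.9 | 0.20 | 0.19 | 5% |

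Estimating the slope costs a little: in simulated data with four arms of 13, the reduction was about 24% at ρ = 0.5 and 13% at 0.7.

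If the follow-up comparisons used raw values at a visit instead of change, the comparator variance would be 1. The reduction would then be 25% at ρ = 0.5 and 49% at 0.7.

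**The case against.** The strongest reply is that T1 is not ignored. It is a level of the mixed ANOVA, and comparing change from T1 between randomised arms is valid and unbiased over repeated randomisations. This stands. A reader might infer from the missing covariate that the planned analysis is biased, or that the baseline tests stand in for adjustment. The document supports neither: the tests and the outcome model are separate choices, and the 0.25 SD shift is conditional on a particular observed gap, not a bias of the method. The covariate is a gain in precision, and it is small where correlation is high.

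A reader might also infer that most reports of such a trial would show false baseline differences. That depends on how many pairs and variables are tested, on the absence of correction and on the correlation between variables, none of which the Protocol states. Independence in particular is implausible for three heads of one muscle plus its force and jump height. For a single variable the figure is about 20%.

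Nor does the plan say that outcomes flagged at baseline would be adjusted afterwards. That is a possible consequence, not a stated step.

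Finally, the variance figures are for a single-visit contrast, not for the 12-df interaction on which the power rests. They show the direction and scale of the gain, not the power of a revised test.

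None of this rescues the baseline sentence. Two-group tests still do not fit four arms, and one four-group test per variable would still test a null that randomisation makes true.

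**Conclusion.** The point holds in two parts of different strength.

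The baseline tests are wrong for the design and uninformative. The size is about 20% per variable if all six pairs are tested uncorrected at 13 per arm, and roughly 61% to 80% over an assumed 7 variables across the readings shown.

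The handling of T1 in the outcome model is valid but less precise than it could be. The single-visit variance reduction runs from 35% at a correlation of 0.3 to 5% at 0.9. It is 25% at 0.5, the value that reproduces the planned total but is not evidence about these outcomes. The reduction holds at every correlation below 1. The change is worth making in a trial this small, but nothing here invalidates the planned analysis.

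**What to change.** Delete the baseline significance tests and show T1 by arm descriptively, without p-values.

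For every outcome, prespecify a repeated-measures analysis of the visits after treatment has been given. Use that outcome's own T1 value, and its interaction with visit, as covariate, whatever imbalance is observed. The response visits are T3 to T5. Include T2 only if it is measured after treatment: the Protocol puts both the T2 assessment and the start of treatment one hour after exercise, so their order has to be stated. Fix all this before unblinding.

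No new data are needed, since T1 is already collected. The costs are one covariate degree of freedom per visit and a new power statement. The stated basis, that "a total sample size of 48 participants is required to achieve the sufficient statistical power", refers to a five-measurement interaction and must be re-run for the revised model at the same sample size, with the assumed correlation written down.

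### The only treatment comparison depends on unnamed assumptions with no stated alternative; the baseline tests do not fit four arms, and T1 is not used as a covariate

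*Protocol*

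**What the plan says.** All of this is in the protocol; no SAP is at hand.

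- **Outcome analysis** (Statistical analysis): "When the assumptions are met, a 5x4 (5 measurements x 4 groups) mixed analysis of variance (ANOVA) will be performed", with Bonferroni correction for multiple comparisons. No other outcome analysis is named.
- **Normality** (same section): "Normal distribution of data will be assessed using histograms and the Shapiro-Wilk test", with p below 0.05 read as non-normal. The consequence is spelled out for summary statistics (median and interquartile range) and for the baseline comparison (Mann-Whitney), but not for the outcome analysis.
- **Baseline** (same section): "Independent t tests or Mann-Whitney U tests will be used to compare means between groups at baseline for quantitative variables". Study Design and Setting defines four groups.
- **Sizing** (Sample size calculation): "An F-test was selected for an ANOVA with repeated measures, accounting for within-between interaction", with "a medium effect size f=0.20, a significance level of 0.05, a power of 0.8, four groups, five measurements" and "a nonsphericity correction of 1", giving 48 participants, raised to 52 for 10% losses.
- **Timing** (Procedure; stimulation protocol under Intervention): T1 is the baseline and T2 to T5 fall 1, 24, 48 and 72 hours after exercise. Treatment also starts one hour after exercise and is labelled T2. The text does not say whether the T2 measurement comes before or after treatment.

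**The concern.** A protocol may leave detail to an SAP. Here, however, it writes a data-dependent rule for its one treatment comparison and fills in only one branch. It recognises that data may be non-normal and provides for that everywhere except where treatment effects are judged. The assumptions could include sphericity, since the sizing takes it as exact and no correction is named. An analysis chosen after seeing the data leaves the error rate of the whole procedure unknown.

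The baseline rule has a different fault. An independent t test or Mann-Whitney test compares two groups, so with four arms it must become a set of pairwise tests, and the Bonferroni phrase is attached to the ANOVA, not to these. Under proper randomisation any difference they find is chance.

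Finally, the T1 value is measured on everyone, yet it serves only as one of five response levels. Using it as a covariate can extract more from the same data.

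**Working it through.** **1. The plan's own figure.** Inputs from Sample size calculation: f = 0.20, alpha = 0.05, k = 4 groups, m = 5 measurements, epsilon = 1. The correlation rho among repeated measures is not given; 0.5 is assumed, with 0.3 and 0.7 as the range.

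- Noncentrality: lambda = f² × N × m / (1 − rho) = 0.04 × 48 × 5 / 0.5 = 19.2.
- Degrees of freedom: (k − 1)(m − 1) = 12 and (N − k)(m − 1) = 176.
- Power = 0.821 at N = 48 and 0.775 at N = 44, so 48 reproduces at rho = 0.5. The required N is 64 at rho = 0.3 and 32 at rho = 0.7.

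**2. How often a normality check trips by chance.** Assume Shapiro-Wilk at 0.05 once per visit on a truly normal outcome. With independent visits: 1 − 0.95⁵ = 0.226. Simulated with correlation 0.5 between visits: about 0.21. This is per outcome.

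**3. Baseline tests.** Four arms give 4 × 3 / 2 = 6 pairs. Simulating six t tests with 13 per arm and no true difference (20,000 runs), at least one p < 0.05 occurs in 0.207 of trials per variable. The value under independence would be 1 − 0.95⁶ = 0.265; it is lower because pairs share arms.

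**4. T1 as response level against T1 as covariate.** Let d be the pattern of the treatment effect over the visits, with compound symmetry.

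- Planned interaction test: information = [Σd² − (Σd)²/5] / (1 − rho).
- Joint test on T2-T5 adjusted for T1: information = [Σd² − (rho/(1 + 4rho))(Σd)²] / (1 − rho). At rho = 0.5, rho/(1 + 4rho) = 1/6.

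| Effect pattern (rho = 0.5) | Planned | T1-adjusted | Ratio | lambda (19.2 × ratio) | Power at N = 48 |
|---|---|---|---|---|---|
| One visit only | 0.8/0.5 = 1.60 | (1 − 1/6)/0.5 = 1.67 | 1.04 | 20.0 | 0.84 |
| Constant T3-T5 | 1.2/0.5 = 2.40 | (3 − 9/6)/0.5 = 3.00 | 1.25 | 24.0 | 0.91 |
| Constant T2-T5 | 0.8/0.5 = 1.60 | (4 − 16/6)/0.5 = 2.67 | 1.67 | 32.0 | 0.98 |

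The adjusted test has 12 and 175 degrees of freedom. Over rho 0.3 to 0.7 the ratio runs from 1.02 to 2.27.

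**5. If the T2 measurement precedes treatment.** The last row cannot then arise, and T2 is not a treatment outcome. Dropping T2 and adjusting T3-T5 for T1 alone replaces 1/6 by rho/(1 + 3rho) = 0.2. The first two rows become 0.8/0.5 = 1.60 and (3 − 9 × 0.2)/0.5 = 2.40, the same as planned. Power is 0.86 in both, only because the test has 9 degrees of freedom instead of 12. At rho = 0.7 with a constant T3-T5 effect, the same formula gives 0.81 of the planned information (power 0.956 against 0.978). Keeping T2 as a second covariate restores the 1/6, and with it the ratios 1.04 and 1.25.

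**The case against.** The best defence is that much of this belongs in an SAP. A fallback, the handling of missing sessions and the choice of covariates may all be there. That stands against a stronger reading: a reader might infer that the trial has no primary analysis. The documents do not show that; they show only that the protocol does not fix what happens if the assumptions fail.

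Other stronger readings also go too far:

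- **That baseline is left out of the outcome analysis, or replaced by the two-sample tests.** T1 is one of the five measurements in the ANOVA, so the group-by-time interaction already reflects change from baseline. The baseline tests are a separate step, and nothing in the text feeds them into a later decision.
- **That the planned test is underpowered or plainly inefficient.** It reaches 0.82 on the protocol's inputs at the assumed correlation. It is less efficient only relative to another model, and if the effect sits at one visit the gain is small.
- **That the ANOVA is expressly gated on Shapiro-Wilk in every group-by-visit cell.** The text speaks of variables, ties the normal/non-normal split to description, and never defines the assumptions. The per-visit figure is therefore itself conditional on a reading.

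What the defence does not remove is the half-written rule, or two-sample tests for a four-arm comparison.

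**Conclusion.** The point holds in a limited form. The missing branch and the mismatch between two-sample tests and four arms can be read directly from the protocol and rest on no assumption. The chance figures assume normality testing once per visit (21-23%) and all six pairs tested without correction (about 21% per variable).

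The gain from adjusting for T1 is a matter of efficiency, not of validity. Its size rests on compound symmetry, a correlation the protocol does not state, and an unknown effect pattern. At 0.5 it is 4% to 67%; the upper end also requires that the T2 measurement follows treatment. If T2 precedes treatment, the gain is 4% to 25% with T2 kept as a covariate, and none in information with T1 alone. The change should be made before analysis, but the trial's design does not depend on it.

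**What to change.** 1. Delete the condition. Make the primary analysis one linear mixed model in SPSS, fitted whatever the data look like, with group, visit, group by visit and T1 as covariate, using all available data. An unstructured covariance avoids a sphericity condition. State which test or contrast is primary.
2. Analyse the visits after treatment: T3-T5, and T2 only if the protocol clarifies that its measurement follows treatment. If it precedes treatment, enter T2 as a second covariate; the calculation above shows that otherwise the gain can disappear.
3. Check residuals as a diagnostic only, not to choose the method.
4. Delete the baseline significance tests and describe baseline by arm.

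The cost is a few sentences and slightly more analysis work in the same software. It needs no new data and no change in sample size.

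### The only planned comparison of the groups after baseline is run only if unlisted assumptions are met, and nothing is named to replace it

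*Protocol*

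**What the plan says.** The Protocol's Statistical analysis section describes one assumption check: "Normal distribution of data will be assessed using histograms and the Shapiro-Wilk test". It then sets a cut-off: "Variables with a p-value less than <0.05 will be considered to have a non-normal distribution", with values above 0.05 taken as normal. The label has one explicit use, the choice of summary statistics: "the median and interquartile range will be reported for non-normally distributed variables". A second use is implied for the baseline comparison: "Independent t tests or Mann-Whitney U tests will be used to compare means between groups at baseline for quantitative variables".

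The treatment comparison follows: "When the assumptions are met, a 5x4 (5 measurements x 4 groups) mixed analysis of variance (ANOVA) will be performed", with Bonferroni correction. The section does not list the assumptions, say how each is judged, or say what is done if one fails.

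The Sample size calculation section ties the trial to this same test: "An F-test was selected for an ANOVA with repeated measures, accounting for within-between interaction".

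**The concern.** A confirmatory test should be certain to be run. Here the only test of whether the groups recover differently depends on a check of the same data, and the Protocol is silent on what happens if that check fails. Mann-Whitney is the only rank test it names. It is named for baseline only, and it compares two groups on one measurement, so it cannot test a group-by-time interaction. If the condition fails, the trial's question either goes untested or is answered by a method picked after seeing the data.

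The check is also a poor basis for the decision. It is applied to variables, whereas the ANOVA's normality assumption concerns residuals. The unit tested (whole variable, visit, or group-by-visit cell) is not fixed, so the chance of a false alarm is not fixed either. In a small cell, a p-value above 0.05 says little about normality.

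**Working it through.** **Inputs from the Protocol (Sample size calculation).** "a medium effect size f=0.20, a significance level of 0.05, a power of 0.8, four groups, five measurements, and a nonsphericity correction of 1"; "a total sample size of 48 participants is required"; 52 recruited, 13 per group. The correlation between visits is not stated. The distribution of CK is not described.

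**Step 1: reproduce the planned figure.** For the within-between interaction with k=4 groups, m=5 visits and ε=1:

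λ = f²·N·m·ε/(1−ρ), df1 = (k−1)(m−1) = 12, df2 = (N−k)(m−1).

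Assume ρ = 0.5.
- N=48: λ = 0.04×48×5/0.5 = 19.2, df2 = 176, power 0.821.
- N=44: λ = 17.6, df2 = 160, power 0.775.

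So 48 is the smallest total with equal groups that reaches 0.80, and the stated figure reproduces. It depends on ρ: the same formula needs 92 at ρ=0 and 24 at ρ=0.8.

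**Step 2: how often the check fails when the data are exactly normal.** Shapiro-Wilk at 0.05 was simulated with 12 or 13 per group (48 or 52 in total) and visit correlations of 0.5 or 0.8. The last column is 1−0.95^j for j independent tests.

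| What must pass | Simulated failure | Independent tests |
|---|---|---|
| One test per variable | about 5% | 5% |
| All 5 visits, groups pooled | about 20% (17% to 23%) | 23% |
| All 20 group-by-visit cells | about 60% (59% to 63%) | 64% |

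**Step 3: effect on the planned power.** Treat the check as independent of the F statistic. The chance that the ANOVA is run and is significant is then 0.82 × (1 − failure rate):
- One test per variable: 0.82 × 0.95 = 0.78.
- Any of 5 visits: 0.82 × 0.77 = 0.63 to 0.82 × 0.80 = 0.66.
- Any of 20 cells: 0.82 × 0.39 = 0.32 to 0.82 × 0.41 = 0.34.

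**Step 4: a skewed outcome.** Assume CK is log-normal. One Shapiro-Wilk test on 52 men rejects in about 60%, 94% and 99.8% of trials at log-SD 0.3, 0.5 and 0.8. In a single cell of 13 the corresponding rates are only about 16%, 34% and 61%. Thus at log-SD 0.5 a cell-level test misses the skew about two times in three, and the rule would then call the data normal.

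**Step 5: what the text offers when the check fails.** The label leads to median and interquartile range (descriptive) and, by implication, to Mann-Whitney (baseline). Neither addresses T2 to T5.

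**The case against.** The strongest reply is that the Protocol never says Shapiro-Wilk decides the ANOVA. The label's only explicit use is descriptive, histograms are used as well, and the assumptions are left open. This is right as far as it goes: the link is inferred. It does not remove the problem, because a condition with no stated criterion is at least as open to a decision made after seeing the data.

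A second reply is that fallbacks, transformations and sphericity corrections belong in a SAP, which is not at hand. The missing fallback alone would indeed not be a finding. The conditional trigger, however, is written into the Protocol, and adding a fallback would still leave the choice of test to a pre-test.

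Several stronger readings are tempting and are not supported:
- **That normal data would usually fail.** This needs the 20-cell reading. The text speaks of variables, and one test per variable fails in only about 5%, a minor loss.
- **That the CK analysis is almost certain to be lost.** The Protocol gives no CK distribution. At log-SD 0.3 with one test the rate is about 60%. CK is also not labelled primary or secondary, although the Procedure section makes CK and lactate the main focus of the muscle-damage evaluation.
- **That non-sphericity would also stop the ANOVA.** No sphericity test is mentioned, and the usual response is a degrees-of-freedom correction, not dropping the test.
- **That the primary electromyography outcome is skewed.** The Protocol defines no amplitude measure and no distribution for it.
- **That a raw-scale ANOVA would be invalid.** In simulated CK data at log-SD 0.8, its type I error was 3.3%. Power for a 40% or 50% reduction was 34% or 62%, against 44% or 75% on the log scale. At log-SD 0.5 there was no difference. The raw analysis can be inefficient under heavy skew, but it is not wrong, which is a reason to run the model always.

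**Conclusion.** The point stands in a limited form. The Protocol makes its only post-baseline group comparison, the one it was sized for, conditional on assumptions it does not list, and it states no alternative for T2 to T5. This is a rule fixed badly and not merely missing detail, and it governs the primary outcome as well as the others.

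The size of the problem depends on an unstated choice, the unit tested; the effective power in Step 3 runs from a small loss to less than half of the planned value. Those figures assume that Shapiro-Wilk decides the ANOVA, that ρ is 0.5 for the planned power, and that the check is independent of the F statistic. The CK figures also assume log-normal data with the log-SDs shown. The core does not depend on any of these values. It should be corrected before the data are analysed.

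**What to change.** Delete the clause that makes the ANOVA conditional, and do not use the Shapiro-Wilk p-value to decide the treatment analysis. State that the group-by-visit model is always run for every outcome, either as the mixed ANOVA with the Greenhouse-Geisser correction always applied or as a mixed model with unstructured covariance. Check residuals by plot. Fix the scale of each outcome before unblinding, for example the natural log for CK, reported as geometric mean ratios. Any analysis prompted by non-normality should be a prespecified sensitivity analysis and not a replacement.

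The cost is a few sentences of wording, with no extra participants or visits. The one drawback is that CK effects, if analysed on the log scale, are reported as ratios instead of differences.
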